14.1 Flowchart FUP study [28](#__RefHeading___Toc137193485)

**LIST OF ABBREVIATIONS AND RELEVANT DEFINITIONS**

| **ABR** | **ABR form (General Assessment and Registration form) is the application form that is required for submission to the accredited Ethics Committee (ABR = Algemene Beoordeling en Registratie)** |
| --- | --- |
| **AE** | **Adverse Event** |
| **AR** | **Adverse Reaction** |
| **CA** | **Competent Authority** |
| **CCMO** | **Central Committee on Research Involving Human Subjects** |
| **CV** | **Curriculum Vitae** |
| **DSMB** | **Data Safety Monitoring Board** |
| **EU** | **European Union** |
| **EudraCT** | **European drug regulatory affairs Clinical Trials GCP Good Clinical Practice** |
| **IB** | **Investigator’s Brochure** |
| **IC** | **Informed Consent** |
| **IMP** | **Investigational Medicinal Product** |
| **IMPD** | **Investigational Medicinal Product Dossier** |
| **METC** | **Medical research ethics committee (MREC); in Dutch: medisch ethische toetsing commissie (METC)** |
| **(S)AE** | **Serious Adverse Event** |
| **SPC** | **Summary of Product Characteristics (in Dutch: officiële productinfomatie IB1-tekst)** |
| **Sponsor** | **The sponsor is the party that commissions the organisation or performance of the research, for example a pharmaceutical**  **company, academic hospital, scientific organisation or investigator. A party that provides funding for a study but does not commission it is not regarded as the sponsor, but referred to as a subsidising party.** |
| **SUSAR** | **Suspected Unexpected Serious Adverse Reaction** |
| **Wbp** | **Personal Data Protection Act (in Dutch: Wet Bescherming Persoonsgevens)** |
| **WMO** | **Medical Research Involving Human Subjects Act (Wet Medisch-wetenschappelijk Onderzoek met Mensen** |

**SUMMARY**

Rationale

150 million children/year suffer from pneumonia worldwide, and 20 million children have to be hospitalized for this reason. Up to 40% of community-acquired pneumonias are caused by Mycoplasma pneumoniae and as many as 34% of cases requiring hospitalization in children. Studies using the recently introduced PCR suggest that M. pneumoniae frequently causes respiratory tract infections (RTI), not only in older children as previously thought, but also in children younger than 5 years. This is important because M. pneumoniae is not sensitive to the first choice β-lactam antibiotics. Moreover, it is unknown whether the detection of M. pneumoniae by PCR also confirms this pathogen as the cause of the infection. A limited number of studies suggest the existence of an asymptomatic carrier state. Due to the shortcomings in diagnosis, knowledge on the role of different host- and bacterial factors on progression to infection is very limited.

Hypothesis

M. pneumoniae is capable of asymptomatic colonization, which can be differentiated from infection by quantitative PCR. M. pneumoniae causes RTI’s in children younger than 5 years as frequently as in older children. The genetic background of M. pneumoniae strains as well as viral co-infections influence progression from colonization to infection.

Objectives

1. To optimize the diagnosis of M. pneumoniae infections by discriminating between colonization and symptomatic infection using quantitative PCR.

2. To study the role of host factors (age, and bacterial and viral co-infection) on infection by M. pneumoniae.

3. To investigate the relationship between M. pneumoniae genotype and virulence.

Study design

Prospective design

Study population

Group A: children with a suspected RTI

Group B: healthy controls

Intervention

Not Applicable.

Main study parameters/endpoints

In this explorative study, M. pneumoniae will be quantified in children aged 0-16 years with mild to severe symptoms of respiratory tract infection, and in a control group consisting of children without respiratory tract infection. The quantity of M. pneumoniae (in copies/ml or copies/swab) will be related to clinical disease in order to differentiate asymptomatic carrier state from infection. To investigate the role of co-colonization or -infection, the presence of other bacteria or viruses in the respiratory tract will be analyzed as well. To study the age distribution in relation to M. pneumoniae infection, a precalculated number of patients of either < 5 or ≥ 5 years of age will be included. Genotyping of M. pneumoniae will be performed, and related to severity of disease and/or colonization. Prevalence of colonization and/or infection with M. pneumoniae will be calculated.

From all study participant the following samples will be obtained:

- Oropharyngeal swab
- Nasopharyngeal swab
- Nasopharyngeal lavage
- Serum

Obtaining these samples is considered common clinical practice. The risks and burden are negligible.

# INTRODUCTION AND RATIONALE

# Lower respiratory tract infections (LRTIs) are among the most common infections in children and adults. The World Health Organization estimates there are 150.7 million cases of pneumonia each year in children younger than 5 years, with as many as 20 million cases severe enough to require hospital admission. Respiratory tract infections are the number one killer in children in developing countries. (1) In children with lower respiratory tract infections, M. pneumoniae is the second most common cause of LRTI after Streptococcus pneumoniae. (2) M. pneumoniae is a human pathogen that causes a range of respiratory infections, such as tracheobronchitis, pharyngitis, and atypical pneumonia. Up to 40% of community-acquired pneumonias are caused by M. pneumoniae and as many as 34% of cases requiring hospitalization in children. (3, 4) Glomerulonephritis, carditis, rhabdomyolysis, Bell palsy, Guillain-Barre syndrome, and acute transverse myelitis are rare complications of M. pneumoniae infection. In addition, infection with M. pneumoniae is associated with both chronic stable asthma and acute exacerbations of asthma. (5) Infection with M. pneumoniae is therefore a major burden of disease. This study has three objectives.

1. A specific diagnosis of the cause of LRTI is important because β-lactam antibiotic treatment of M. pneumoniae infections is ineffective, due to the lack of a cell wall, whereas the use of antibiotics such as macrolides can markedly reduce the duration of the illnesses. (6) While the clinical diagnosis of LRTI is usually relatively straightforward, determining the etiological diagnosis can be much more difficult due to the limitations of conventional diagnostic tests, and because of difficulty in obtaining adequate sputum samples for culture in children. As culture of M. pneumoniae is slow and insensitive, the laboratory diagnosis has largely relied on serological testing. Although there have been recent improvements, the sensitivity and specificity of antibody detection is suboptimal. In addition, it often only provides a retrospective diagnosis of acute infection because a convalescent serum specimen is needed to show a fourfold increase in titre. Serologic testing is therefore not optimum for patient management, however this is still used as golden standard for M. pneumoniae detection. (7)

More recently, polymerase chain reaction (PCR) demonstrated the potential to produce rapid, sensitive and specific results, and is now considered the method of choice for direct pathogen detection. (8) However, there is justified concern when the PCR assay is used as the sole means of detection without culture, serology, or clinical data, because surveillance studies using culture and/or PCR indicate that a prolonged asymptomatic carrier state may occur in some persons. (9-12) Since it is not known whether there is a specific threshold quantity of M. pneumoniae in respiratory tract tissues that can differentiate asymptomatic carrier state from infection, a positive result by PCR may overestimate the clinical importance, and may result in unnecessary use of antibiotics. On the other hand, if quantitative PCR will demonstrate to be a reliable technique for diagnosing M. pneumoniae infection, M. pneumoniae will be diagnosed more often. This will result in more adequate treatment of RTI’s in children. It has been suggested that children colonized with M. pneumoniae might be an unrecognized reservoir for the spread of this pathogen. (12) The application of quantitative PCR assays will be crucial in optimizing diagnosing RTI by M. pneumoniae, and in gaining a better understanding of the carrier state associated with M. pneumoniae. Therefore, this is one of the main objectives of our study.

1. M. pneumoniae is thought to be a pathogen that causes pneumonia in children aged 5 years and older. Choice of treatment is based on this supposed age-distribution. Since M. pneumoniae is not susceptible to β-lactam antibiotics, a macrolide antibiotic is the first choice treatment in this age-group. In children younger than 5 years, β-lactam antibiotics are the first choice treatment, because M. pneumoniae is presumed to be a rare cause of RTI in this age-group. However, data on age distribution are conflicting. (13) Specialized diagnostic techniques showed that M pneumoniae might have a more important role in causing both upper and lower respiratory tract infections than previously thought; they seem to be frequent also in children aged less than 5 years. (4, 14) To address this issue, we will investigate the rate of infection among children belonging to different age groups.

In addition, we will study the role of bacterial and viral co-infections. Co-infections can account for up to 30-50% of the cases of M pneumoniae infection. (4, 15, 16) Infection with M. pneumoniae is frequently associated with infections with S. pneumoniae and respiratory viruses. This association might be due to damage to the respiratory epithelium by a virus facilitating infection with M. pneumoniae. However, virtually nothing is known regarding this issue. Children younger than 5 years frequently suffer from viral respiratory infections, which might support the data that M. pneumoniae infections in this age-group are more frequent than previously thought. It is also unknown whether viral co-infection leads to more severe clinical disease. This study aims to answer these questions.

1. A crucial step in the initiation of infection by M. pneumoniae is its attachment to the respiratory epithelium (cytadherence). This process is essential to pathogenesis since mutants that are unable to adhere are also avirulent.(17) Cytadherence is mediated by a specialized and complex attachment organelle. This organelle is localized at the tip of the bacterium and consists of a network of adhesins and accessory proteins. The major adhesion protein (cytadhesin) that is concentrated in the attachment organelle is the surface-exposed, 170-kDa P1 protein. Apart from its function in binding to the respiratory epithelium, the P1 protein is known to elicit a strong humoral immune response during infection. (18) In relation to its immunodominance, the P1 protein was hypothesized to undergo antigenic variation on the basis of the presence within its gene of sequences of which multiple variants exist throughout the M. pneumoniae genome. (19, 20) It is therefore possible that recombination between the P1 gene and these sequences elsewhere in the genome could generate significant sequence variation within the P1 gene, resulting in amino acid changes in the P1 protein at the bacterial surface. This proposed mechanism for antigenic variation of P1 may provide a means for M. pneumoniae to escape from host immune responses. (21) Our research group in the Laboratory of Pediatrics aims to design a definitive, universal system for typing of M. pneumoniae strains on the basis of the P1 sequences, and to understand antigenic variation of the P1 protein. Together, we will aim to elucidate the relationship between M. pneumoniae virulence and P1 antigenic variation using the collected samples, and clinical data.
2. **OBJECTIVES**

Our objectives are to:

1. Optimize the diagnosis of M. pneumoniae infections by differentiating between asymptomatic colonization and infection using quantitative, real-time PCR
2. Study host factors for infection with M. pneumoniae (age distribution of children suffering from M. pneumoniae infections, and the role of co-infection with common bacterial pathogens, and respiratory viruses)
3. Determine the influence of genotypic differences between M. pneumoniae strains on virulence.

# STUDY DESIGN

**Aim I: To optimize the diagnosis of M. pneumoniae infections using quantitative PCR**

We will initiate our investigations in a well-defined and easy accessible study population. Children visiting the Emergency Department of the Erasmus Medical Center/Sophia Children’s Hospital in Rotterdam because of suspected respiratory tract infection will be asked to participate in this study. Since this department has an open environment, many children present with symptoms of both upper and lower respiratory tract infections, submitted by a general practitioner as well as by themselves or their parents. In fall 2009 the recruitment of group A will be extended by pediatric patients attending the General Practitioner’s Service, in this protocol referred to as HAP (Huis Artsen Post).

Group B, consisting of healthy controls, will be recruited from children undergoing surgery at the Erasmus MC/ Sophia Children’s Hospital. Many children need to have surgical procedures for reasons that are not in any way related to the exclusion criteria of our study. These children, who have not suffered from an RTI over the previous two weeks and who have not used antibiotics in the preceding 48 hours, are considered eligible for inclusion. The main reason to address these children instead of approaching schools and day care centres is the fact that children undergoing a surgical procedure are drugged by anaesthetics anyway. This way the burden for healthy controls will be minimized.

*Clinical samples*

From each patient the following samples will be obtained

- Oropharyngeal swab
- Nasopharyngeal swab
- Nasopharyngeal lavage
- Serum (blood sample of 200 microliters)

In group A second serum samples will be taken 2-3 weeks after the first visit.

*Clinical data*

For each patient, patient characteristics, time of onset of illness, clinical signs and symptoms, use of antibiotics, laboratory results and radiological findings, treatment, complications, and hospitalization will be documented in a standardized questionnaire. Based on clinical data different diagnosis will be made. This will be divided in lower respiratory tract infections (such a pneumonia and bronchiolitis) and upper respiratory tract infections (such as pharyngitis). Severity of disease will be determined by days of required oxygen or mechanical ventilation.

*Detection of M. pneumoniae*

All swabs will be washed out in a buffer, which allows bacterial culturing as well as total nucleic acid (DNA and RNA) purification. Material will be frozen at -80C and analyzed as a batch. Purified nucleic acids will be used in real-time PCR assays for the detection of M. pneumoniae.

M. pneumoniae will be detected and quantified using a quantitative, real-time (TaqMan®) PCR assay that has recently been developed in the Laboratory of Pediatrics by Dr. [name].

RTI by M. pneumoniae will be defined by RTI symptoms in combination with serology and/or culture positive for M. pneumoniae and/or conventional PCR for M. pneumoniae.

Aim II: To study the role of host factors (age, and bacterial and viral co-infection) on infection by M. pneumoniae

*Approach*

See aim I

*Clinical samples*

See aim I

*Clinical data*

See aim I. Virulence will be defined by disease severity (determined by hospitalization and duration of hospitalization).

*Detection of M. pneumoniae and other bacteria and viruses:*

See aim I. The other bacteria that will be investigated are S. pneumoniae, Staphylococcus aureus, Haemophilus Influenzae and Moraxella catarrhalis. These bacteria will be detected using routine, conventional bacterial culturing. In collaboration with the department of virology ([name]. [name]), the following respiratory viruses will be detected by real-time PCR: influenzaviruses, parainfluenzaviruses, rhinoviruses, respiratory syncitial virus (RSV), coronaviruses and human metapneumovirus (hMPV).

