# STATISTICAL ANALYSIS

Research questions and analysis

Question 1 (objective 1): does asymptomatic carrier state with M. pneumoniae exist (see question 3, we expect to find > 10%, using quantitative PCR) (10), and if so, can asymptomatic carrier state be differentiated from infection using quantitative PCR?

Analysis: in children with respiratory tract infections caused by M. pneumoniae (as defined by positive standard PCR, positive serology, and or positive culture, group A), results from the quantitative PCR (results in copies/ml) will be compared with the results from the quantitative PCR in asymptomatic children (healthy asymptomatic children with positive results from either standard conventional PCR or culture, group B) using the Mann-Whitney U test. A PCR value, which can differentiate asymptomatic carrier state from infection (threshold), will be determined using Receiver Operating Characteristic (ROC) curves. This value should have a high sensitivity and acceptable specificity.

Question 2 (objective 1): what is the sensitivity and specificity of this quantitative PCR?

Analysis: sensitivity and specificity will be determined using Receiver Operating Characteristic (ROC) curves. In addition we will investigate the sensitivity and specificity according to whether the quantitative PCR results in a positive or negative result (lowest possible detecting range is 10 copies).

Question 3 (objective 1): what is the prevalence of asymptomatic carrier state?

Analysis: prevalence of asymptomatic carrier state (a positive result with quantitative PCR) will be calculated in group A (children with a positive quantitative PCR result and RTI not caused by M. pneumoniae) and B (healthy asymptomatic children with a positive PCR result). We expect to find >10% in group B (10).

Question 4 (objective 2): does M. pneumoniae infection occur more often in children older than 5 years?

Analysis: children in group A with a RTI caused by M. pneumoniae will be divided in two groups, according to age (< 5 years and ≥ 5 years) and compared to each other, with respect to the prevalence using 2-test.

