### Study design

## *Approach*

Children enrolled in the study as described under Aim I in chapter 3, may participate in the follow up study if they tested positive for *M. pneumoniae* by either real time PCR or culture in a sample taken during the first visit. The results of the tests taken during the first visit will be made available to parents and participants about one week prior to the second visit. Subsequently they will be asked to participate in the following protocol

*Definitions*

1. Children with RTI in combination with the presence of *M. pneumoniae,* as detected by either culture or real-time PCR in either the oropharyngeal swab or the nasopharyngeal lavage taken during the first visit, i.e. **group A+** or **group HAP+**. (Note: these children not necessarily suffer from disease caused by infection with *M. pneumoniae*. The gold standard for *M. pneumoniae* infection in this study is serology in combination with standard PCR.)

2. Healthy children tested positive for *M. pneumoniae* by culture or real-time PCR in either the oropharyngeal swab or the nasopharyngeal lavage taken during the first visit, i.e. **group B+**.

*Follow up protocol*

In the follow up protocol participants will be tested for the presence of *M. pneumoniae* in the nasopharynx and oropharynx once a month during a maximum period of one year or until they test negative in both tests (culture and real-time PCR) on two successive occasions. For monthly sample collections, either house-calls will be performed or participants may visit the emergency department of the Erasmus MC – Sophia, whichever is most convenient for participants at that time. If a child, participating in this study, suffers from a RTI during the follow up period, he/she will be evaluated, during daytime, by a physician specialized in pediatric infectious diseases. At all times during the follow up study, parents are free to take him/her to their own general practitioner. For emergencies parents should follow the normal procedures.

*Clinical samples*

Each month a nasopharyngeal lavage and an oropharyngeal swab will be taken and real-time PCR and culture will be performed for *M. pneumoniae* as described previously in chapter 3. Test results will be made available to the participants and their parents every month since these results determine whether the study is continued for each participant individually.

*Clinical data*

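### The protocol gives two incompatible definitions of M. pneumoniae infection; the one used in the main analysis counts PCR-positive carriers with another RTI as cases

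*Protocol*

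**What the plan says.** Section 3 (Study design, Aim I, Detection of M. pneumoniae) fixes the case definition: "RTI by M. pneumoniae will be defined by RTI symptoms in combination with serology and/or culture positive for M. pneumoniae and/or conventional PCR". Section 9 (Statistical analysis, Question 1) repeats it for the cases: "as defined by positive standard PCR, positive serology, and or positive culture, group A". Their comparators are "healthy asymptomatic children with positive results from either standard conventional PCR or culture, group B".

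Section 12.1.3 (ancillary study, Definitions) takes group A children who are positive by culture or real-time PCR and notes that "these children not necessarily suffer from disease caused by infection with" M. pneumoniae. It then says that the gold standard for M. pneumoniae "infection in this study is serology in combination with standard PCR".

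Three further statements bear on this:

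- Section 9, Question 3 counts carriers within group A as "children with a positive quantitative PCR result and RTI not caused by M. pneumoniae". For healthy children it says: "We expect to find >10% in group B".
- Section 9, Question 2 says that "sensitivity and specificity will be determined using Receiver Operating Characteristic (ROC) curves", without naming a reference standard.
- Section 1 warns that, because carriage exists, a positive PCR can overstate clinical relevance and lead to unnecessary antibiotics.

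**The concern.** Telling carriage from infection is the first main endpoint (section 7.1). A case definition that one positive PCR can satisfy treats every PCR-positive child with respiratory symptoms as infected, and so settles in advance the question the study asks. The case group then contains some of the carriers it is meant to be separated from, and the ROC threshold in Question 1 is estimated on that mixture.

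Question 3 depends on the same definition, because a carrier in group A exists only if the RTI is classed as not caused by M. pneumoniae. Questions 4 to 6 use the same case set. If Question 2 uses it too, quantitative PCR is scored against a reference that includes another PCR for the same organism.

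**Working it through.** **1. The definitions side by side.** Consider a group A child with conventional PCR positive, serology negative and culture negative.

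- Sections 3 and 9: RTI caused by M. pneumoniae, because one positive test suffices.
- Section 12.1.3: does not meet the gold standard, because serology is also required.

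The same child is a case under one rule and not under the other.

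**2. Effect on Question 3.** Under the any-one-of rule, a group A carrier must be positive by quantitative PCR and negative by conventional PCR, by culture and by serology. The category therefore measures disagreement between assays at least as much as carriage.

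**3. Effect on Question 1.** Group A cases can enter on serology alone, with no copies detected. Group B children must be positive by conventional PCR or culture. The two arms are selected by different rules.

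**4. The plan's own figure that rests on the definition.** Section 4.4 and Question 4 state a detectable difference of 12 points with 400 and 100 children and 10% infection below 5 years. For 10% versus 22%, two-sided α 0.05, normal approximation:

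- pooled rate = (40 + 22)/500 = 0.124; null SE = √(0.124 × 0.876 × (1/400 + 1/100)) = 0.0368
- alternative SE = √(0.10 × 0.90/400 + 0.22 × 0.78/100) = 0.0441
- z = (0.12 − 1.96 × 0.0368)/0.0441 = 1.08, so power is about 86%

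The figure is reasonable as it stands. But its 10% and 12 points mean something only once the infection definition is fixed.

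**5. Size of the dilution (illustration).**

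Inputs:
- Total PCR positivity in group A, T = 10%. Section 12.1.4 expects 10% positive RTI, and its sample size paragraph reports about 10% of enrolled children PCR positive.
- Carriage among children with another RTI, c: not given in the protocol, so varied over 2%, 5% and 8%.
- Assumed: PCR detects all infected children and all carriers; carriers with another RTI have the same load as healthy carriers; the true AUC for infected versus carrier is 0.90.

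Formulas, with i the true infection rate:
- T = i + (1 − i)c, so i = (T − c)/(1 − c)
- carrier share of labelled cases, f = (T − i)/T
- apparent AUC = (1 − f) × 0.90 + f × 0.50 = 0.90 − 0.40f

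| c | i | f | carriers among 50 labelled cases (n = 500) | apparent AUC |
|---|---|---|---|---|
| 2% | 0.08/0.98 = 8.2% | 18% | 9 | 0.83 |
| 5% | 0.05/0.95 = 5.3% | 47% | 24 | 0.71 |
| 8% | 0.02/0.92 = 2.2% | 78% | 39 | 0.59 |

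With a true AUC of 0.80 the last formula becomes 0.80 − 0.30f, giving 0.74, 0.66 and 0.57.

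**The case against.** **Scope.** The gold-standard sentence is a parenthetical note in the ancillary section, where the study named may be the ancillary one. The scope is indeed loosely worded. However, the ancillary children come from groups A and B, and the follow-up protocol collects lavage and oropharyngeal swabs but no serum. The serology in the note can only be the main study's.

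**PCR alone.** A reader might infer that the main study defines infection by PCR alone. It does not. Serology and culture also count; PCR is one sufficient route.

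**Question 3 empty.** One might conclude that the group A carrier category is empty by construction. That would require conventional PCR to detect nearly everything quantitative PCR detects. The protocol gives no relative sensitivity, and low-load carriers could still fall in the category. It is restricted, not shown to be empty.

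**Question 2 circular and sensitivity inflated.** No reference is named for Question 2, the two PCRs are different assays, and nothing states that they use the same material. Incorporation bias follows only if the main case definition is the reference. Even then the net direction is open, because serology-only cases with zero copies lower sensitivity.

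**All positives are carriage.** With 10% positive in both groups, one might argue that carriage explains every group A positive. Section 12.1.1 reports a seemingly higher load in RTI patients, which argues against this. The figure above 10% in section 9 is also a quantitative PCR expectation for healthy children. Applying 10% carriage to ill children on top of 5% to 20% true infection would imply 14.5% to 28% positivity in group A, which does not match the protocol's roughly 10%.

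**Serology is imperfect.** Section 1 says so. A stricter rule will place some missed infections among the probable carriers. This stands, and is a reason to report that group separately and to keep the wider definition as a sensitivity analysis.

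**Conclusion.** The contradiction is explicit and affects the first main endpoint. As written, the any-one-of rule counts PCR-positive carriers with another RTI as cases, against the protocol's own warning about PCR. It dilutes Question 1 and its threshold, restricts the group A carriage count in Question 3 and carries into Questions 4 to 6. Question 2 is exposed to incorporation bias if it uses the same definition, with the net direction uncertain.

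The size depends on a carriage rate that the protocol does not give. Over 2% to 8%, the carrier share of labelled cases runs from about 18% to 78%, and a true AUC of 0.90 would appear as about 0.83 down to 0.59. These figures rest on 10% total positivity in group A, complete detection by PCR and equal load in both kinds of carrier. They illustrate the mechanism and are not estimates. The conflict needs resolving before analysis, whatever the carriage rate turns out to be.

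**What to change.** Reconcile section 3 (Aim I), section 9 and section 12.1.3.

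- **Questions 1 and 3 to 6:** take serology together with standard PCR, as in section 12.1.3, as the primary case definition. Report PCR-positive, serology-negative group A children separately as probable carriers.
- **Question 2:** name a reference that contains no PCR, namely paired serology with or without culture. It has to differ from the case definition above, because that definition includes PCR.
- **Sensitivity analysis:** repeat the analyses under the any-one-of definition.
- **Sample size:** restate the 10% infection rate and the 12-point detectable difference (section 4.4 and Question 4) for the chosen definition.

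No new samples are needed, since first and second sera are already planned in group A. The costs are fewer cases, children without a second serum who may be unclassifiable, and some true infections missed by serology and reported as probable carriers. The selection rules in Question 1 will still differ, because healthy carriers must be found by PCR or culture and group B gives only one serum. Serology-only cases with zero copies would, however, no longer enter the primary comparison.
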